#### Lifestyle and Behavior Change Education Component

The education component will also take place at the UNSW Medicine and Health Lifestyle Clinic and involve group discussions developed by a health psychologist and delivered by a health and clinical psychologist. The education topics and resources are presented in Table 3. In summary, they include information about living with osteoarthritis and cognitive decline, PA, nutritional advice, psychological health, social connections, developing individual goals and action plans, and final sessions determined by individual or group preferences. Educational materials are presented in the resources column of Table 3 and have been developed by organizations, including Dementia Australia, Arthritis New South Wales, Alzheimer’s Association, and the Australian Government Department of Health. Printed and electronic copies will be provided to participants and used to guide discussions.

### Statistical Analysis and Clinical Interpretation

Feasibility, acceptability, and preliminary efficacy of the program will be analyzed. Feasibility will be examined by assessing group session attendance, quantified as total sessions attended out of a maximum possible and reported as a percentage. Feasibility will be quantified as session compliance with criteria for success, requiring performance of at least 10 minutes of aerobic training and 5 progressive resistance training exercises per session. Participant attendance, exercise programming, and adverse events will be recorded. Reasons for nonattendance will be collected and reported. Adverse events will be recorded, and ongoing monitoring and reporting will be completed in accordance with CONSORT guidelines [48]. Acceptability will be determined by participants’ perspectives and experiences of the program based on final participant feedback (focus groups or interviews). Acceptability will encompass what participants liked most and least about the program and their suggestions for the content and format of the sessions. Preliminary efficacy of the program will involve analysis of health outcomes (QoL, cognition, and psychological health). Quantitative data will be analyzed using SPSS Statistics (version 30.0.0.0, 172), with normality checks and descriptive statistics for frequencies and distributions. Baseline data will be compared between control and intervention groups to ensure there are no significant differences between groups at baseline. Health outcomes will be compared pre- and postprogram completion and between the intervention and control groups using 1-tailed *t* tests and repeated measures ANOVAs. Statistical significance will be set to *P*<.05. Effect sizes will be calculated using Cohen *d* for *t* tests and ηp^2^ for ANOVAs. Results will be reported comparing the intervention versus the waitlist control group and before versus after the 12-week program. Qualitative data will be analyzed using thematic content analysis [47].

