### Objectives

We will pilot the evidence-based Healthy Body and Mind Program (HBMP), which includes PA, nutrition, lifestyle, and behavior change education on health outcomes in people living with cognitive decline and osteoarthritis. The evidence base for development of the program is outlined in Figure 1. The primary aims of this pilot randomized controlled trial (RCT) are to determine (1) the feasibility (ie, recruitment, retention, and adherence) of the HBMP for people living with osteoarthritis and cognitive decline in a community clinic and the University of New South Wales (UNSW) Medicine and Health Lifestyle Clinic, Sydney, Australia, and (2) the acceptability of the program to people living with osteoarthritis and experiencing cognitive decline. The secondary aim is to obtain pilot data on health outcomes in people with osteoarthritis and cognitive decline, following the program when compared to usual care. Health outcomes are QoL, cognition, pain, psychological health (depression, anxiety, and stress), and physical health (weight, waist circumference, blood pressure, cardiorespiratory fitness, strength, mobility, and balance). We hypothesize that individuals who complete the program will have better health outcomes when compared to the baseline and the control groups.

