
### Study Design

This 12-week pilot RCT of the HBMP with a waitlist control group will use quantitative and qualitative research methodologies. Data collection will comprise the following: (1) clinical observations routinely completed as part of standard care (eg, clinical interviewing, physical assessment, and exercise monitoring), (2) validated patient-reported outcome measures (including QoL, cognition, pain, and psychological health), and (3) focus group or interviews (Table 1). Clinical observations and questionnaires will be completed at baseline (0 wk) and after intervention (12 wk). Initial community and stakeholder engagement has assisted in developing the group program and ensuring it is feasible and acceptable to participants. The study team includes accredited exercise physiologists (AEPs), accredited practicing dietitians, a health psychologist, and research assistants (RAs). All study activities will take place within the UNSW Medicine and Health Lifestyle Community Clinic facilities.

**Table 1 table1:** Data collection methods and outcome measures.

Measure or tool		Procedure (tools or guidelines)

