Following successful screening, the participant will be allocated a unique ID number using the generated list. The RA who performs the randomization will advise the data collectors of the participants’ IDs by referring to the password-protected spreadsheet of participant names and allocated ID numbers. After completion of baseline testing, participants will be randomly assigned to the intervention (n=10) or waitlist control groups (n=10) using a computer-generated randomization list produced by a researcher external to the study group. In total, 20 participants will complete the program. After completing a 12-week period of usual care, those in the waitlist control group will then complete the 12-week HBMP. A 12-week follow-up will be performed to examine sustainability. Participants are allowed to withdraw from the trial at any time they wish and are assured that doing so would not alter their care or relationship with the university or the community clinic.

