#### Health Outcomes

Baseline and postintervention assessment visits will take between 90 and 120 minutes, including the health interview, physical assessment, and questionnaire completion. The RA completing assessments will be blinded to the condition (intervention or waitlist control groups). The RA will be trained and supervised by an AEP.

Secondary outcome measures will be completed before randomization at baseline and 12 weeks after intervention. The outcome measures (questionnaires outlined in the subsequent section) will be completed by an RA and a member of the research team who is blinded to the group allocation. Health outcome measures will include QoL (measured using the Short Form Health Survey-36) [46]; cognition (MoCA [36] and the Cambridge Neuropsychological Test Automated Battery attention, learning, and memory tasks); pain (Western Ontario and McMaster Universities Osteoarthritis Index) [44,52]; psychological health (Depression, Anxiety, and Stress Scale-21) [45]); and physical health (weight, waist circumference, blood pressure, functional fitness, strength, mobility, and balance). Balance exercises will be simple easy to perform movements that take place in a purposefully designed environment that minimizes the risk of falls (ie, they will be beside a wall, with an AEP closely monitoring them and simple exercises will be completed first, enabling the AEP to continually assess whether it is safe for the participant to continue to the slightly more challenging balance exercises).

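### Health outcomes are compared without using their pre-randomization values as covariates, baseline balance is judged by significance test, and the before-after tests have no control

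*Protocol article*

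**What the plan says.** The section Statistical Analysis and Clinical Interpretation sets three things.

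- On baseline: "Baseline data will be compared between control and intervention groups to ensure there are no significant differences between groups at baseline".
- On the tests: "Health outcomes will be compared pre- and postprogram completion and between the intervention and control groups using 1-tailed" t tests and repeated measures ANOVAs, at P<.05, with Cohen d and partial eta squared as effect sizes. No covariate is named.
- On reporting: "Results will be reported comparing the intervention versus the waitlist control group and before versus after the 12-week program". Neither comparison is named as the main one.

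The Objectives section pairs the same two comparisons: "We hypothesize that individuals who complete the program will have better health outcomes when compared to the baseline and the control groups". The Health Outcomes section shows that a baseline value exists for each outcome: "Secondary outcome measures will be completed before randomization at baseline and 12 weeks after intervention". The Recruitment section allocates 10 participants to each group. The Results section reports 18 enrolled, with their data collection complete, as of October 2025.

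**The concern.** The randomized week-12 comparison is the only one in this trial in which the groups differ by chance and treatment alone. In a sample of 18 to 20 it should be estimated as precisely as the collected data allow. The plan has the pre-randomization value of each outcome but does not use it as a covariate.

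Instead, the baseline values serve in a significance test meant to assure balance. After randomization any baseline difference is due to chance, so the test has no hypothesis to examine. At this size a non-significant result says little about whether the groups are alike.

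The before-after tests answer a different question from the randomized contrast. Repeated cognitive testing (MoCA and the computerized battery), the passage of time and regression to the mean can all produce improvement without any program effect. If such change is read as benefit, the pilot passes a misleading signal to the larger trials that it is meant to inform.

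**Working it through.** **Inputs.** 10 per group (Recruitment); 0.5 SD as the minimal important difference (Sample Size Calculation); 1-tailed t tests at .05 (Statistical Analysis). The pre-post correlation r is not given, so a range is assumed. Equal SDs at both times are assumed. The baseline test is taken as two-sided, because the article does not say.

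**The plan's own figure.** n per group = 2(z₀.₉₇₅+z₀.₉₀)²/d² = 2(1.960+1.282)²/0.5² = 84.1, so 85. This matches the stated 85 per group and corresponds to an unadjusted comparison (variance factor 1 below).

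**1. Precision.** In units of 2σ²/n, the variance of the estimated group difference is:

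- week-12 values only: 1
- change score, which is also the ANOVA group-by-time test: 2(1−r)
- ANCOVA: (1−r²)(1+1/(N−4)); at N=20 the last factor is 1+1/16 = 1.0625

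| r (assumed) | change | ANCOVA | ANCOVA/change | ANCOVA/week-12 only |
|---|---|---|---|---|
| 0.3 | 1.40 | 0.967 | 0.69 | 0.97 |
| 0.5 | 1.00 | 0.797 | 0.80 | 0.80 |
| 0.7 | 0.60 | 0.542 | 0.90 | 0.54 |
| 0.8 | 0.40 | 0.382 | 0.96 | 0.38 |
| 0.9 | 0.20 | 0.202 | 1.01 | 0.20 |

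The ratios to the change score at r=0.5 and 0.7 equal about 25% and 11% more participants (1/0.797 and 1/0.903). Break-even with change scores: (1+r)/2 × 1.0625 = 1, so r = 0.88. Break-even with week-12 only: 1−r² = 1/1.0625, so r = 0.24.

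With 18 participants the factor is 1+1/14 = 1.071. The ratios to the change score become 0.75×1.071 = 0.80 and 0.85×1.071 = 0.91, with break-even at r = 0.87.

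Simulation of 40,000 trials at 10 per arm agrees. Variances in SD² for week-12 only / change / ANCOVA were 0.199/0.200/0.158 at r=0.5 and 0.199/0.120/0.108 at r=0.7. Two-sided power at 0.5 SD was 18%/19%/22% and 19%/28%/30%; type I error was about 5% for all three.

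For the full trial at 90% power, n per arm would be 85/85/64 at r=0.5 and 85/51/43 at r=0.7.

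**2. Baseline test at 10 per arm.**

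- Smallest significant difference: t₀.₉₇₅,₁₈ × √(2/10) = 2.101 × 0.447 = 0.94 SD.
- Power when the true difference is 0.5 SD: 18%.
- Chance of an observed imbalance of at least 0.5 SD under randomization: 2[1−Φ(0.5/0.447)] = 26%. At most 5% of trials are flagged, so at least 26−5 = 21% carry such an imbalance unflagged, for any one outcome.
- Effect of a 0.5 SD imbalance: a week-12-only estimate shifts by 0.5r, that is 0.25, 0.35 and 0.40 SD at r=0.5, 0.7 and 0.8. A change-score estimate shifts the other way by 0.5(1−r), that is 0.25, 0.15 and 0.10 SD.

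**3. Before-after test.** Assume no program effect and the same improvement in both arms, from practice or regression to the mean. The size of that improvement is an assumption. Share of trials in which the 1-tailed paired test in 10 participants is significant:

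| common improvement | r=0.5 | r=0.7 | r=0.8 |
|---|---|---|---|
| 0.2 SD | 14% | 18% | 24% |
| 0.3 SD | 23% | 30% | 40% |

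The between-group tests stay at about 5% in all these settings.

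**The case against.** The strongest reply is that the precision point concerns efficiency, not error. That stands: the planned between-group tests hold their type I error, and the gain in two-sided power at 0.5 SD over the change score is only 2 to 3 percentage points. Health outcomes are secondary pilot data, the Discussion concedes that they may not reach significance, and feasibility and acceptability are untouched. It might also be said that covariates belong in an analysis plan. Here, though, the article names its tests, so this is a stated choice that can be improved.

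Several stronger readings are tempting, and the documents do not support them.

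- A reader might infer that ANCOVA always beats the change score. That is a large-sample result; at N=20 the lost degree of freedom cancels the gain near r=0.88. The large-sample ratio (1+r)/2 would suggest 33% and 18% more participants at r=0.5 and 0.7, which overstates the 25% and 11% found here.
- A reader might infer that chance imbalance goes wholly uncorrected. The group-by-time test subtracts baseline, so it over-corrects instead. Only a week-12-only t test ignores baseline, and the article does not say that its t test is of that kind.
- A reader might infer that before-after results have formally equal weight. The article lists both comparisons under the same tests and threshold and ranks neither; it says no more.
- A reader might infer that the waitlist group lacks a post-program visit, or that the follow-up is a comparison without a comparator. The article says only "A 12-week follow-up will be performed to examine sustainability", without fixing time or arm. It does not say that waitlist participants enter the before-after analysis, and it plans no between-group test at follow-up. The timing is unclear, not shown to be absent.

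**Conclusion.** The point holds as a worthwhile improvement to a secondary analysis; it does not make the trial invalid. For r between 0.5 and 0.7, ANCOVA reduces variance by about 20% to 10% against the group-by-time or change-score test, and by about 20% to 46% against a week-12-only t test. These figures rest on assumed correlations, equal SDs and 10 per arm; with 18 participants they barely change. There is no gain over change scores at about r=0.88 or above, and none over week-12-only below about r=0.24.

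The baseline significance test is the clearest fault, because it cannot do what the article asks of it at any sample size and has little power at this one. The before-after tests cannot separate program effect from practice, time or regression to the mean. The 14% to 40% range depends on the assumed common improvement of 0.2 to 0.3 SD.

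**What to change.** - Estimate the week-12 between-group difference for each health outcome by ANCOVA, with randomized group and the same measure at baseline as terms, and report it with a 95% CI. State openly that this change was made after data collection.
- Replace the baseline significance tests with a descriptive table by group.
- Label before-after and follow-up results as descriptive, and do not present them as evidence of a program effect.

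The cost is one model degree of freedom and changed analysis wording. The baseline values are already collected. No further assessment visit is asked for: data collection is complete for the 18 enrolled.

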### Adverse Events

PA may cause concern in older adults and people living with chronic conditions. Adverse events may occur (eg, a fall), despite the safety protocols we have put in place (eg, AEP or RA closely monitoring participants during exercise in a purposefully designed clinic or laboratory setting with handrails). Throughout the trial and follow-up, adverse events will be documented, and risk will be continually assessed by appropriately trained professionals (ie, AEP). Reported adverse events will include details about the type of event, date, time, and duration; severity (mild to severe); whether it could have been avoided; outcome (solved to fatal); and whether it was related to the study (certainly, probably, possibly, unlikely, or cannot say). The relevant ethics committee and participant’s general practitioner will be informed about any serious event (eg, requiring hospitalization) that takes place during the study. Adverse events will be reported transparently alongside study outcomes. In accordance with the CONSORT (Consolidated Standards of Reporting Trials) statement [48] and similar to other studies [53], data from participants who are suspended from the trial due to an adverse event will be entered into the analysis by their allocated treatment group. The lead researcher will continue to communicate and support the participant and signpost them to relevant support services where appropriate. An independent safety monitoring process has been established (the data safety monitoring board) to oversee participant safety and review this trial. These arrangements have been documented in a safety monitoring plan, reviewed and approved by the human research ethics committee. All research staff involved in this trial have completed training and certification in Good Clinical Practice guidelines.

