## Results

As of October 2025, we have enrolled 18 participants and completed their data collection. Results are expected to be published during the first quarter of 2026.

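### The repeated measures ANOVA leaves out a suspended participant who has no week-12 value, in tension with the rule that such participants' data are analysed in their allocated arm

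*Protocol article*

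**What the plan says.** Statistical Analysis and Clinical Interpretation names the software ("Quantitative data will be analyzed using SPSS Statistics (version 30.0.0.0, 172") and compares health outcomes before and after the program, and "between the intervention and control groups using 1-tailed *t* tests and repeated measures ANOVAs". Besides the t tests, the only method named is "repeated measures ANOVAs"; the section names no model that can use a participant with only one of the two values.

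Adverse Events sets an as-allocated rule of limited scope: data from those "suspended from the trial due to an adverse event will be entered into the analysis by their allocated treatment group".

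Study Design gives two assessment times: "Clinical observations and questionnaires will be completed at baseline (0 wk) and after intervention (12 wk"). Data Collection and Outcome Measures repeats this schedule. Recruitment adds a later visit, "A 12-week follow-up will be performed to examine sustainability", after describing how the waitlist arm takes the program once its control period ends. The analysis section does not place that visit in the ANOVA.

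On numbers, Recruitment plans 10 per arm, and Results states "As of October 2025, we have enrolled 18 participants and completed their data collection".

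**The concern.** A standard repeated measures ANOVA needs a full row of values for each person. With two visits, anyone lacking the week-12 value is deleted, including their baseline. A before-after paired t test has the same requirement. If a participant is suspended for an adverse event and is not assessed at week 12, the stated method removes that person, whereas the Adverse Events section says that the person's data go into the analysis by allocated arm.

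At stake is whether the between-arm estimates of the health outcomes, which are meant to inform larger trials, describe everyone randomised or only those who reached week 12. If people with worse pain, mood or cognition at baseline are more likely to leave one arm, a completers-only estimate is shifted.

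**Working it through.** **Step 1. The two statements side by side**

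| Participant | Adverse Events rule | Repeated measures ANOVA |
|---|---|---|
| Suspended, week-12 value present | Data enter as allocated | Included; no tension |
| Suspended, week-12 value absent | Data (the baseline) enter as allocated | Deleted |

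Only the second row is a problem. The article does not say whether it will occur.

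**Step 2. Where the attrition rate comes from**

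The only rate given is 15%-20%, in Sample Size Calculation. The figure there of 85 per group reproduces: 0.5 SD, two-sided 5% and 90% power give 85. Then 85 × 1.20 = 102 per group, or 204 in total. The rate therefore belongs to the future full-scale trial. Using it for this pilot is an assumption:

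- 20 planned: 20 × 0.15 = 3.0 to 20 × 0.20 = 4.0 people without week 12.
- 18 enrolled: 18 × 0.15 = 2.7 to 18 × 0.20 = 3.6 people.

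**Step 3. Precision**

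A simulation (6,000 runs per setting, two visits, true effect 0.5 SD) compared the completers-only difference in change, which is what the ANOVA's arm-by-time term estimates, with a likelihood-based estimate of the same contrast that keeps every baseline. With N = 20, 20% dropout at random and an assumed correlation of 0.5, the SD of the estimate is 0.502 for completers only and 0.495 when the dropouts' baselines are kept. The ratio is 0.495/0.502 = 0.986, a gain of about 1.4%. Baseline adjustment is a separate matter: a completers' analysis adjusted for baseline has an SD of 0.453 in the same setting, but that gain does not come from keeping the dropouts.

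**Step 4. Bias**

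Assumed mechanism: control-arm dropout is random at rate d. In the intervention arm, those with a baseline below the mean drop out at rate 2d and the others do not, so the arm average is still d. Baseline is standard normal and has correlation r with week 12.

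Among intervention-arm completers the mean baseline is √(2/π) × d/(1−d) = 0.798 × d/(1−d). The change score depends on baseline with slope r − 1, so the completers-only bias is −(1−r) × 0.798 × d/(1−d). For d = 0.20 and r = 0.5 this is −0.5 × 0.798 × 0.25 = −0.100.

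| N | d | r | Formula | Simulated, completers only | Simulated, all baselines kept |
|---|---|---|---|---|---|
| 18 | 0.15 | 0.5 | −0.070 | −0.080 | −0.010 |
| 18 | 0.15 | 0.7 | −0.042 | −0.043 | −0.001 |
| 18 | 0.20 | 0.5 | −0.100 | −0.098 | 0.004 |
| 18 | 0.20 | 0.7 | −0.060 | −0.053 | 0.006 |
| 20 | 0.15 | 0.5 | −0.070 | −0.066 | 0.006 |
| 20 | 0.15 | 0.7 | −0.042 | −0.045 | −0.003 |
| 20 | 0.20 | 0.5 | −0.100 | −0.096 | 0.001 |
| 20 | 0.20 | 0.7 | −0.060 | −0.056 | 0.005 |

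The simulation error of a bias is about 0.5/√6000 = 0.006. Completers-only bias is therefore about 0.04 to 0.10 SD, at most a fifth of the true 0.5 SD (0.10/0.5), and it is close to zero once all baselines are used.

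**The case against.** The strongest reply is that no two stated rules collide. The Adverse Events sentence concerns the arm in which data are counted. It covers adverse-event suspensions only and does not say that these people skip week 12. The analysis section does not say that only complete cases are used, and missing-data handling may stand in a full protocol or analysis plan that is not shown. This part stands: a reader might infer a flat contradiction, and the text supports only a tension that arises if a suspended participant has no week-12 value. Silence on missing data is not the point either. The point is that the method actually named cannot use such a participant.

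It can also be said that repeated measures ANOVA is a standard choice for two arms and two visits, that the outcomes are secondary in a feasibility pilot, and that the bias is small beside the imprecision. With 9 per arm (an assumed even split of the 18) the 95% half-width for a standardised difference is t(16) × √(2/9) = 2.12 × 0.471 = 1.00 SD. All of this stands and keeps the point modest.

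Two stronger readings are tempting:

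- A reader might infer that the ANOVA costs precision, since the half-width grows from 1.00 SD at 9 per arm to 1.12 SD at 7.5 per arm. That compares full data with data after dropout. The week-12 values are missing under any model, so changing the model does not recover the loss.
- A reader might infer that the sustainability follow-up forms a third time point, so that valid week-12 data are lost when that visit is missed. The analysis section describes a comparison of before with after the 12-week program, and the follow-up is never put into the ANOVA.

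**Conclusion.** The point holds as a cheap improvement. Followed as written, the ANOVA would drop a suspended participant who lacks week 12, and the Adverse Events section says that such a participant's data are analysed as allocated. The benefit of changing is fidelity to that rule and protection from bias when dropout depends on observed baseline values: about 0.04 to 0.10 SD under the mechanism, dropout rates and correlations assumed above, none of which the article gives for this pilot. Precision from retaining dropouts is practically unchanged.

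Whether anyone is affected is unknown. The article reports 18 enrolled with data collection completed, which neither establishes nor rules out missing week-12 values. If there are none, the tension has no practical effect.

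**What to change.** Replace the between-arm repeated measures ANOVA with a linear mixed model (SPSS MIXED):

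- Data: baseline and week-12 values of all randomised participants, in their allocated arm, whether or not week 12 was obtained.
- Fixed effects: visit and arm-by-visit with a common baseline mean (no arm difference at baseline). Alternatively, keep separate baselines and report the arm-by-visit contrast. The raw week-12 difference from a model with separate baselines should not be the result, because it ignores chance baseline imbalance with about 9 to 10 per arm.
- Inference: an unstructured covariance for the two visits and a stated small-sample degrees-of-freedom method such as Satterthwaite or Kenward-Roger.
- Report: the estimated week-12 difference with its 95% CI, and the number per arm without a week-12 value.
- Keep the follow-up after the waitlist arm has taken the program out of this randomised comparison.

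A baseline-adjusted analysis of completers had a similarly small bias in the simulation, but it would still leave out the suspended participant's data.

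Cost: analysis wording only, in the same software and with no new data. The downsides are that a degrees-of-freedom method must be chosen and that the result relies on missing-at-random. Because data collection is reported as completed and preliminary findings have been presented (Dissemination), the change should be dated and declared when results are reported.

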**Objective:**

This study aims to examine the feasibility, acceptability, and health outcomes following the 12-week Healthy Body and Mind Program, designed for people with osteoarthritis who are experiencing cognitive decline. The findings will inform the designs of larger trials.

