### Sample Size Calculation

For pilot trials, using a 90% 1-sided CI, it is estimated that a sample size should be at least 9% of that calculated for a fully powered RCT [49]. Given a minimal clinically important difference of 0.5 SD (medium effect size), QoL measured using the Short Form Health Survey-36 [50], α of .05 (with Holm-Šídák correction), and power of 90% (β=.20) for a 2-group comparison, the required sample size would be approximately 85 participants per group (170 total). Accounting for potential dropout or attrition (15%-20%), 102 participants per group (N=204 total) would need to be recruited for a fully powered trial, and 16 participants would be required for a pilot trial. This study aims to recruit 20 participants.

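### Partial eta squared at about 9–10 per arm averages 0.05–0.06 with no effect at all, about the value of the plan's own 0.5 SD important difference; Cohen d is only mildly inflated

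*Protocol article*

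**What the plan says.** Under Statistical Analysis and Clinical Interpretation, the article compares health outcomes before and after the programme and "between the intervention and control groups using 1-tailed *t* tests and repeated measures ANOVAs". The next commitment is: "Effect sizes will be calculated using Cohen" d for the t tests and partial eta squared for the ANOVAs. These are named estimators, so the choice is made in the text.

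The sample is small. The Recruitment section assigns 10 participants to each arm, and the Results section reports: "As of October 2025, we have enrolled 18 participants and completed their data collection". The split of the 18 between arms is not given.

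On the role of these figures, the Objectives section says: "The secondary aim is to obtain pilot data on health outcomes in people with osteoarthritis and cognitive decline". Feasibility and acceptability are the primary aims. The abstract's Objective adds: "The findings will inform the designs of larger trials". The one full-trial calculation, under Sample Size Calculation, starts from a fixed target: "Given a minimal clinically important difference of 0.5 SD (medium effect size").

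**The concern.** Partial eta squared is a proportion of variance and cannot be negative, so chance variation alone pushes its average above zero. With fewer than 20 error degrees of freedom that push is not small. Cohen d divides by an estimated standard deviation, and this inflates its average by a factor that grows as the degrees of freedom fall.

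What is at stake is how the preliminary-efficacy results are read. The article concedes under Anticipated Findings that improvements may not reach significance with so few participants, so readers will tend to look to the effect sizes. If a programme with no effect typically yields a partial eta squared close to that of an important difference, the statistic cannot do the descriptive job given to it.

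**Working it through.** **Inputs.** 10 per arm (Recruitment), so the error df for a two-arm comparison are 20 − 2 = 18. 18 enrolled (Results); assuming 9 per arm, 16 error df. Minimal important difference 0.5 SD (Sample Size Calculation).

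**The plan's own figure.** With d = 0.5, two-sided α = 0.05 and 90% power, n per group = 2 × (1.960 + 1.282)² / 0.5² ≈ 84.1, rounded up to 85. This reproduces the stated 85 per group and shows that the full-trial size rests on 0.5 SD and on no pilot estimate.

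**Partial eta squared, 1-df effect.** In a two-arm, two-time-point ANOVA the group-by-time effect is the two-sample t test on change, with F = t² on 1 and df error degrees of freedom, and partial eta squared = F / (F + df).
- Average with no effect: 1 / (df + 1), which is 1/19 = 0.053 at 18 df and 1/17 = 0.059 at 16 df.
- Population value at d = 0.5 with equal arms: d² / (d² + 4) = 0.25 / 4.25 = 0.059.
- Average when d = 0.5 is true (1,000,000 simulated F values per setting): 0.106 at 10 per arm and 0.112 at 9 per arm.

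Here d is in SD units of the score analysed. For change scores with equal variances and pre-post correlation r, the SD of change is √(2(1 − r)) times the outcome SD, so 0.5 outcome SD equals 0.5 change SD only at r = 0.5. A higher r raises the population value and a lower r reduces it. The averages with no effect do not depend on r.

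**Alternatives in the same simulations.** For a 1-df effect, omega squared = (F − 1) / (F + df + 1) and epsilon squared = (F − 1) / (F + df).

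| True d | Population value | Partial eta squared | Omega squared | Epsilon squared |
|---|---|---|---|---|
| 0 | 0 | 0.053–0.059 | about 0 | about 0 |
| 0.5 | 0.059 | 0.106–0.112 | 0.054 | 0.056 |

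**Cohen d.** The average of d is the true value divided by J(df) = Γ(df/2) / [√(df/2) Γ((df − 1)/2)].

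| Comparison | df | J | Inflation |
|---|---|---|---|
| Between arms, 10 per arm | 18 | 0.958 | 4.4% |
| Between arms, 9 per arm | 16 | 0.952 | 5.0% |
| Pre-post in one arm of 10 | 9 | 0.914 | 9.4% |
| Pre-post in one arm of 9 | 8 | 0.903 | 10.8% |
| Pre-post, both arms pooled, 20 | 19 | 0.960 | 4.2% |
| Pre-post, both arms pooled, 18 | 17 | 0.955 | 4.7% |

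The pre-post rows take d as mean change over the SD of change. Between arms, a true 0.50 averages 0.50/0.958 = 0.522 to 0.50/0.952 = 0.525.

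**Bias in d against its imprecision.** At an observed d of 0.5, SE = √(2/n + d²/(4n)). For n = 10 this is √(0.2 + 0.00625) = 0.454, giving a 95% CI of −0.39 to 1.39. For n = 9 it is 0.479, giving −0.44 to 1.44.

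**The case against.** The strongest reply is that this is a reporting preference about a secondary statistic. Cohen d and partial eta squared are widely understood and contradict nothing else in the article. The between-arm bias in d, about 0.02, is trivial beside an interval nearly 1.8 wide. Intervals and small-sample corrections are details that an article may leave to an analysis plan not shown. Much of this stands. The absence of an interval is not counted as a fault here, and the bias in between-arm d would not justify a comment by itself. What remains is the named choice of partial eta squared, whose bias is as large as the quantity of interest.

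A reader might go further and infer that these effect sizes are the figures meant to set the size of the larger trial, which would then be too small. The article does not support that. The abstract speaks of findings in general, health outcomes are a secondary aim, and the only full-trial calculation uses a prespecified 0.5 SD. Inferring a shortfall from the pre-post d would also mean sizing a two-group trial on a single-arm, paired effect, which the article nowhere proposes.

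The 9%–11% figure for d also depends on the reading. The waitlist group later completes the programme, so the before-versus-after analysis may pool both arms, and the inflation is then 4%–5%.

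Finally, omega squared has its own cost. With no effect, F falls below 1 about two-thirds of the time, so the estimate is then negative. Truncating it at zero would bring back upward bias.

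**Conclusion.** A minor point, and an optional improvement. Followed as written, the plan would on average report a partial eta squared of 0.053–0.059 for a programme with no effect, about the 0.059 that corresponds to its own 0.5 SD important difference, and about 0.11 when that difference is real. The upward bias in Cohen d is real but small: 4%–5% between arms, and 9%–11% only if pre-post tests are run within a single arm. These results assume 1-df effects, roughly equal arms of 9–10, and 0.5 SD expressed in units of the score analysed. They concern how preliminary efficacy is described, and they have no bearing on the feasibility aims or the stated full-trial sample size.

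**What to change.** In Statistical Analysis and Clinical Interpretation, replace partial eta squared with partial omega squared (or epsilon squared), reported without truncation at zero, and replace Cohen d with Hedges g. Give the raw mean difference alongside, each with a 95% CI. State whether the before-versus-after effect size is calculated within one arm or pooled over both, since this determines the correction.

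The cost is one line of analysis wording and no new data: omega squared and epsilon squared follow from F and its degrees of freedom, and g is d multiplied by J. The price is smaller reported effects (slightly so for d) and frequent negative omega squared values when there is no effect, which need a short note to readers. The full-trial calculation needs no change on this account.
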